### Participants

Participants will be sequentially recruited from the Canadian HPS Program Database between late 2019 and approximately mid-2023 (including a pause due to SARS-COV-2 for much of 2020). The eligibility criteria are outlined in Table 2. The drop-out criteria are provided under the “Exercise protocol” section.

**Table 2 Tab2:** Eligibility criteria

**Inclusion criteria** 1. Moderate HPS: (a) Liver disease (evidence of synthetic liver dysfunction and/or portal hypertension on biochemistry and/or imaging) (b) Moderate hypoxemia ▪ PaO_2_ < 80 mmHg ▪ AaDO_2_ ≥ 15 mmHg or ≥ 20 mmHg if age > 64 [1] (c) Intrapulmonary vascular dilatations (microbubbles seen in the left heart ≥ 3 cycles after the right heart on saline contrast echocardiography) 2. Presence of orthodeoxia (PaO_2_ decrease by > 4 mmHg when the patient moves from supine to upright position) **Exclusion criteria** 1. Pulmonary hypertension (a) Echocardiographic estimated right ventricular systolic pressure ≥ 50 mmHg (b) Right heart catheterization mean pulmonary artery pressure > 25 mmHg with pulmonary capillary wedge pressure ≤ 15 mmHg 2. Significant obstructive ventilatory impairment (FEV1/FVC ratio < 0.65) [14] 3. Known significant coronary artery disease 4. Significant neurologic, orthopedic, or rheumatological disorders preventing the use of a cycle ergometer 5. Other absolute contraindications to submaximal exercise testing [24] (a) Uncontrolled cardiac arrhythmia with hemodynamic compromise (b) Symptomatic severe aortic stenosis (c) Decompensated heart failure (d) Acute cardiopulmonary illness (e.g., venous thromboembolism, myocarditis, pericarditis, endocarditis, acute aortic dissection) 6. Moderate or severe ascites	

*PaO*_*2*_ partial pressure of arterial oxygen, *FEV1/FVC* forced expiratory volume in 1 s over forced vital capacity, *AaDO*_*2*_ alveolar-arterial oxygen gradient [PAO_2_ − PaO_2_, where PAO_2_ = [FiO_2_ (*P*_atm_ − *P*_H2O_) − PaCO_2_/0.8]], *AO*_*2*_ partial pressure of alveolar oxygen, *FIO*_*2*_ inspiratory oxygen fraction, *P*_*atm*_ atmosphere pressure, *P*_*H2O*_ water vapor partial pressure, *PaCO*_*2*_ arterial carbon dioxide pressure

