^†^Univariate analyses are presented for each variable, continuous variables assessed with a 2-sample *t*-test, and categorical variables with a chi-squared test. Variables were assessed on the same day as orthodeoxia or within an interval of ≤ 1 year

To our knowledge, this is by far the largest analysis of both the prevalence and risk factors for orthodeoxia in HPS. Given that patients with orthodeoxia had more severe hypoxemia, it was not surprising that our more “severe” HPS cohort (compared to other reports) had a high observed orthodeoxia prevalence of 66.1% (Table 3). We complimented this with an analysis of our current active HPS database, revealing that six patients currently meet the inclusion criteria. Additionally, a review of referrals in the last 3 years reveals that an average of 4 eligible patients is referred to our program each year. Based on a recruitment target of 50%, this analysis of the Canadian HPS Program Database suggests that we will be able to recruit 10 eligible participants to this study in the 4-year recruitment window allowed by study funding. We believe that this target is achievable, particularly with our pessimistic 50% recruitment target, since patients with HPS and orthodeoxia have no effective treatment options other than liver transplant, the study involves nearly no risk, and the study offers an opportunity to identify a clinically beneficial exercise strategy for the individual.

A crossover design has previously been successfully employed in patients with HPS [30]. The advantage of the crossover design in rare diseases such as HPS is that each participant will undergo both interventions, and within-person comparisons will limit confounding and reduce inter-subject variability, thereby reducing the sample size required to demonstrate an effect [38]. The crossover design is well-suited to an exercise intervention because there is no anticipated therapeutic carryover effect, obviating the need for a washout (we allowed for a 1-day minimum “washout” period for recovery from the prior exercise test). We established a 4-week maximum period between tests to minimize any possible period effect (i.e., to prevent significant disease progression by the time of the second test). The possibility of a period effect due to familiarity with the cycling exercise will be evaluated statistically.

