Calculating the demonstrable effect size in this sample (10 participants) requires an estimate of the standard deviation of the expected change in stopping time between supine and upright positions. However, due to the novelty of this study design, there is no existing literature investigating supine exercise in patients with HPS. We also did not find any studies comparing supine and upright exercise in patients with cirrhosis without HPS. However, we did identify a study that employed a crossover design to evaluate the effect of hyperoxia (which has a similar physiologic impact to supine position in our cohort) on CWRET stopping time [39], in patients with interstitial lung disease—a condition in which the primary abnormality is a reduced diffusion capacity, which may have a comparable physiologic impact on exercise as the diffusion-perfusion defect of HPS. This study showed that exercise time increases significantly with hyperoxia compared to room air (21.9 ± 12.9 vs 11.6 ± 10.0 min, *P* < 0.001) [39], with a pooled standard deviation for change in exercise duration of 11.5 min. Applying this standard deviation, our crossover trial with a target sample size of 10 participants will be able to detect a difference of ≥ 2.85 min between the two interventions with power of 80% and a two-sided alpha of 0.05.

An increase in exercise time of 2.85 min is clinically meaningful in other hypoxemic diseases. In COPD, the minimal clinically important difference (MCID) for tLIM on CWRET is an increase of 33% or 105 s from baseline [26]. Bronchodilator trials suggest that clinical outcome improvements correspond to tLIM improvements of > 60 s [26]. Accordingly, an improvement of 2.85 min (171 s) would likely be clinically significant in our participants, who have more severe baseline exercise limitations than typical patients with COPD. With an estimated upright test duration of 3–8 min in our design [26], a change of 2.85 min would represent an improvement of between 36 and 95%, which again suggests a clinically meaningful improvement.

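### The detectable difference of 2.85 min does not follow from the stated SD of 11.5 min with 10 participants: those inputs give about 11.5 min, and power for 2.85 min is about 11%, not 80%

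*Protocol article*

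**What the plan says.** All of this is in the Protocol article, Recruitment and power. The sample size was set by feasibility, and the plan then asks whether the effect that 10 participants can show is plausible and clinically meaningful. It says that this needs the SD of the change in stopping time between positions. For that it turns to a crossover study of hyperoxia against room air in interstitial lung disease, where exercise time was 21.9 ± 12.9 against 11.6 ± 10.0 min, "with a pooled standard deviation for change in exercise duration of 11.5 min". The plan says that it applies this SD, and that "our crossover trial with a target sample size of 10 participants will be able to detect a difference of" 2.85 min or more, "with power of 80% and a two-sided alpha of 0.05".

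The next paragraph builds on the result. It converts 2.85 min to 171 s, compares this with a COPD minimal important difference of 105 s or 33%, and says that with an upright test of 3–8 min "a change of 2.85 min would represent an improvement of between 36 and 95"%.

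**The concern.** For a paired comparison with 10 participants, 80% power and two-sided 0.05, the detectable difference is roughly one SD of the within-person change. An SD of 11.5 min therefore cannot sit beside a detectable difference of 2.85 min; the two differ by a factor of about four (11.5 / 2.85 = 4.04).

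The figure carries weight. Because the number of participants came from feasibility, the only quantitative support for it is the claim that the detectable effect is small enough to be plausible and large enough to matter. The 171 s, the comparison with 105 s and the 36–95% range all rest on 2.85 min. If it is wrong, a reader is told that the trial has 80% power for an effect for which, on the plan's own inputs, it has about 11%.

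**Working it through.** **Inputs (Recruitment and power).** n = 10, each participant tested in both positions; SD of change 11.5 min; power 80%; two-sided alpha 0.05; source-study SDs 12.9 and 10.0 min. The Statistical analysis section adds a period term to the model, which reduces the error degrees of freedom from 9 to 8.

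**1. Trying to reproduce 2.85 min.** The detectable difference is k × SD of change. From the noncentral t distribution, k = 0.996 at n = 10 with 9 df and 1.012 with 8 df. The normal approximation gives k = (1.960 + 0.842)/√10 = 0.886.

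| Reading of 11.5 min | Detectable difference (min) |
|---|---|
| SD of change, t, 9 df | 0.996 × 11.5 = 11.45 |
| SD of change, t, 8 df (period term) | 1.012 × 11.5 = 11.64 |
| SD of change, normal approximation | 0.886 × 11.5 = 10.19 |
| SD of change, one-sided 0.05 | 9.81 (t), 9.04 (normal) |
| Per-test SD, correlation 0 (SD of change 11.5√2) | 16.20 (t), 14.41 (normal) |
| 11.5/√2 | 8.10 (t), 7.20 (normal) |
| 20 observations counted as n | 7.20 (normal) |
| Two parallel groups, 10 or 5 per arm | 14.4 or 20.4 (normal) |
| 11.5 misread as a variance, two-sided | 3.38 (t), 3.00 (normal) |
| 11.5 misread as a variance, one-sided | 2.89 (t), 2.67 (normal) |

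None of these returns 2.85 min. Only the variance readings come near, and they contradict the text, which calls 11.5 min an SD; the two-sided version still does not match.

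**2. Power for 2.85 min.** The standardised difference is 2.85/11.5 = 0.248 and the noncentrality is 0.248 × √10 = 0.784. Two-sided power is 10.8% with 9 df, 10.7% with 8 df and 12.0% by normal approximation.

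**3. Participants needed for 2.85 min at 80% power.** Normal approximation: ((1.960 + 0.842) × 11.5/2.85)² = 127.8, so 128. With the t distribution: 130.

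**4. What 11.5 min is.** √((12.9² + 10.0²)/2) = √((166.41 + 100)/2) = √133.2 = 11.54. This is the pooled SD of exercise time across people in the two conditions. An SD of within-person change also needs the correlation r between a person's two tests: SD of change = √(12.9² + 10.0² − 2 × r × 12.9 × 10.0). The document does not give r, so the values below are assumptions.

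| Assumed r | SD of change (min) | Detectable difference, t, 9 df (min) | Power for 2.85 min |
|---|---|---|---|
| 0.5 | 11.7 | 11.7 | 11% |
| 0.7 | 9.3 | 9.2 | 14% |
| 0.8 | 7.7 | 7.7 | 18% |
| 0.9 | 5.8 | 5.8 | 28% |

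**5. SD that 2.85 min would need.** 2.85/0.996 = 2.86 min (9 df), 2.85/1.012 = 2.82 min (8 df), 2.85/0.886 = 3.22 min (normal). The document gives no SD of change in the range 2.8 to 3.2 min.

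**The case against.** The strongest objection is that 11.5 min should not be called the correct detectable difference. If 11.5 min is really a pooled per-test SD, then a detectable difference of 11.5 min is only what a mislabelled input implies, and it agrees with the two-SD calculation only near r = 0.5. This stands. The source tests averaged 11.6 and 21.9 min, while the Exercise protocol section targets 180–480 s, so the SD of change in this trial may be much smaller and the design may do better than these figures suggest.

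For the same reason, a reader might infer that the trial can only detect an effect longer than the whole expected 3–8 min upright test. The documents do not support that: it divides an SD from long tests by the length of short ones.

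A reader might also infer that 2.85 min is mathematically out of reach, since the SD of change from 12.9 and 10.0 cannot fall below 12.9 − 10.0 = 2.9 min, which gives 0.996 × 2.9 = 2.89 min. That bound holds only with those two unequal SDs and an exact t calculation. With a common SD of 11.5 min, 2.85 min is reached at r of about 0.97; with the unequal SDs and the normal approximation, at r of about 0.992. Such correlations are implausible and are not claimed in the plan, but they are not impossible.

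Finally, 10 participants were chosen for feasibility, so correcting the figure changes neither recruitment nor conduct. That is true, but it makes the power statement the only numerical defence of the sample size. None of these points restores the sentence, because the plan says explicitly which SD it applied.

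**Conclusion.** Wrong as written. On the stated inputs the detectable difference is about 11.5 min (10.2 to 11.6 min by method) instead of 2.85 min, and power for 2.85 min is about 11% instead of 80%. This rests only on the plan's own SD, sample size, power and alpha, with a paired analysis. The mislabelling of 11.5 min is inferred from its exact match with the pooled condition SD. The range of 5.8 to 11.7 min rests on assumed correlations of 0.9 down to 0.5.

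The finding is about the stated justification. It does not show that the trial is too small for its purpose, because the document holds no SD of within-person change for tests of this length. Nor does it support a claim that recruitment will fall short: the Participants section mentions a pause for much of 2020, but the number of active recruitment years would have to be assumed.

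**What to change.** Replace the sentence in Recruitment and power in one of two ways:

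- Keep 11.5 min as the SD of change, and report that 10 participants detect about 11.5 min with 80% power and that power for 2.85 min is about 11%.
- State, as an explicit assumption, an SD of the paired difference suited to 3–8 min tests, and tabulate the detectable difference with the period term in the model: about 1.01 × SD at n = 10, 1.09 × SD at n = 9 and 1.19 × SD at n = 8. The smaller numbers are useful because the Primary outcome measure section removes some participants from the analysis.

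In either case, show the calculation and correct the label: 11.5 min is the pooled SD of the two conditions unless the source supports calling it an SD of change. Withdraw the 171 s and 36–95% argument, or recompute it from the new figure.

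The cost is a rewritten paragraph and a less favourable stated figure. No extra patients and no change to the conduct of the trial are needed.

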### Recruitment and power

Given that HPS is a rare disease, and a majority of patients progress to either liver transplant or death relatively soon after diagnosis [10], recruitment to prospective trials in HPS has previously proven very challenging [30, 31]. Our recruitment will be further limited by the fact that only a subset of patients with HPS has orthodeoxia. Accordingly, we first estimated a recruitment target based on feasibility then set out to determine whether the demonstrable effect size with this sample would be both plausible and clinically meaningful. To estimate feasible recruitment, we searched the literature for studies describing the prevalence of orthodeoxia in cohorts of ≥ 10 HPS patients. However, we found only 4 small reports (14–20 patients each) reporting a highly variable prevalence of orthodeoxia, ranging from 14 to 88% of HPS participants (Table 3).

**Table 3 Tab3:** Characteristics of orthodeoxia in patients with hepatopulmonary syndrome

Author	Mean upright^†^ PaO_**2**_ (mmHg)	Prevalence of orthodeoxia^‡^, ***N*** (%)	Mean room air PaO_**2**_ in patients with orthodeoxia (mmHg) (SD)	Orthodeoxia (supine PaO_**2**_ − upright PaO_**2**_; mmHg)
Krowka et al., 1993 [32]	44.0	14/16 (87.5)	Upright: 44.0 ± 9 Supine: 62.0 ± 14	18.0
Martinez et al., 1999 [33]	65.2	2/5 (40.0)	Upright: 51.0 ± 3 Supine: 61.5 ± 2	10.5
Martinez et al., 2001 [34]	75.0	2/14 (14.3)	Upright: 63.5 ± 21 Supine: 71.5 ± 21	8.0
Gomez et al., 2004 [35]	69.0	5/20 (25.0)	Upright: 59.0 ± 6 Supine: 67.0 ± 5	8.0
Current study*	51.8	37/56 (66.1)	Upright: 48.1 ± 14 Supine: 61.9 ± 12	13.8

*Analysis performed in patients at the Toronto site of the Canadian HPS Database with a PaO_2_ < 80 mmHg, absence of significant concurrent lung disease contributing to hypoxemia, and absence of concurrent portopulmonary hypertension

^†^All studies defined “upright” as the sitting position, except for Krowka 1993 [32] and the current study, which defined it as the standing position

^‡^All studies defined orthodeoxia as a drop in partial pressure of arterial oxygen (PaO_2_) of greater than 5% or 4 mmHg in the upright compared to the supine position, except Martinez 1999 [33], which defined it as a drop in PaO_2_ greater than 10 mmHg in the upright compared to the supine position

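### The detectable difference of 2.85 min does not follow from the stated inputs, which give about 11.5 min; power at 2.85 min is about 11%

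*Protocol article*

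**What the plan says.** All the relevant text is in the protocol article, Methods and design, Recruitment and power. Recruitment is limited by the rarity of the disease, so the authors fixed the sample by feasibility and then "set out to determine whether the demonstrable effect size with this sample would be both plausible and clinically meaningful".

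They say the calculation "requires an estimate of the standard deviation of the expected change in stopping time between supine and upright positions". They take that SD from a crossover study of hyperoxia in interstitial lung disease, where exercise times were "21.9 ± 12.9 vs 11.6 ± 10.0 min". The article reports this result "with a pooled standard deviation for change in exercise duration of 11.5 min". It applies that SD to 10 crossover participants and puts the smallest detectable effect at "2.85 min between the two interventions with power of 80% and a two-sided alpha of 0.05".

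The next paragraph defends 2.85 min (171 s) as clinically meaningful. It compares it with a COPD threshold of 105 s and notes that, against an upright test of 3–8 min, "a change of 2.85 min would represent an improvement of between 36 and 95" per cent.

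**The concern.** Every input to the calculation is printed, and so is its result, but the two do not agree. The standard error of the mean difference is 11.5/√10 = 3.64 min. A true difference of 2.85 min is therefore only 0.78 standard errors, far below what 80% power requires.

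This is more than a misprint in a side remark. Because the sample size came first, the detectable difference is the only statistical argument that the trial is worth running at that size. If the figure is wrong, so is the claim of 80% power at a clinically meaningful effect. A non-significant result could then be read as evidence against a benefit of about 3 min that the trial, on its own inputs, had little chance of detecting.

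**Working it through.** **Inputs (Recruitment and power, unless noted)**
- n = 10 participants, each tested in both positions
- SD of change = 11.5 min
- power 80%, two-sided alpha 0.05
- stated result: 2.85 min
- source study: means 21.9 and 11.6 min, SDs 12.9 and 10.0 min
- the Statistical analysis section adds a period term, leaving 8 rather than 9 degrees of freedom

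**Step 1. Reproduce the stated figure.**
SE = SD/√n = 11.5/√10 = 3.64 min.
- Normal approximation: (1.960 + 0.842) × 3.64 = 10.19 min
- Paired t, 9 df (noncentral t): 11.45 min, which is 0.996 × SD
- Period-adjusted, 8 df: 11.64 min

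The stated 2.85 min is 2.85/11.45 = 25% of the paired-t result. It is not reproduced.

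**Step 2. Power at 2.85 min on the same inputs.**
- 10.8% (9 df), 10.7% (8 df), 12.0% (normal)
- Participants needed for 80% power at 2.85 min: 130 (t) or 128 (normal)

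**Step 3. Look for another reading that gives 2.85 min.**

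| Reading | Detectable difference (min) |
|---|---|
| One-sided alpha | 9.0 (normal), 9.8 (t) |
| 11.5 as within-subject SD (SD of change 11.5√2) | 14.4 (normal), 16.5 (t) |
| 20 observations treated as independent | 7.2–7.6 |
| Parallel groups, 10 per arm / 5 per arm | 15.2 / 23.3 |
| 11.5 read as a variance | 3.00 (normal), 3.38 (t) |
| SD/n used in place of SD/√n | 3.2–3.7 |

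None gives 2.85.

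**Step 4. What SD would give 2.85 min?**
The SD of change would have to be 2.86 min (t, 9 df), 2.82 min (t, 8 df) or 3.22 min (normal).

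The printed 11.5 agrees with the two condition SDs pooled: √((12.9² + 10.0²)/2) = 11.54. Suppose, then, that it is a per-condition SD and that within-person correlation ρ reduces it:
- Equal SDs of 11.5: SD of change = 11.5√(2(1 − ρ)), so ρ must be about 0.96 (normal) to 0.97 (t).
- Cited SDs: SD of change = √(12.9² + 10.0² − 2ρ × 12.9 × 10.0). At ρ = 1 this is 2.9 min, already above 2.86, so the t calculation cannot reach 2.85 min at any correlation. The normal approximation reaches it at ρ of about 0.99.

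No correlation is stated. For assumed values with the cited SDs (t, 9 df):

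| Assumed ρ | Detectable (min) | Power at 2.85 min |
|---|---|---|
| 0.5 | 11.7 | 11% |
| 0.7 | 9.2 | 14% |
| 0.8 | 7.7 | 18% |
| 0.9 | 5.8 | 28% |

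**Step 5. Consequences on the stated inputs.**
- Smallest significant observed mean difference: 2.262 × 3.64 = 8.2 min (9 df), longer than the upper end of the 3–8 min target. The normal approximation gives 1.960 × 3.64 = 7.1 min.
- Detectable gain as a share of upright time: 11.45/8 = 143% to 11.45/3 = 382%, against the stated 36–95%.
- Gain in the source study: 21.9 − 11.6 = 10.3 min. Power for that gain is 71% (t, 9 df) or 81% (normal).

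**Step 6. Range over assumed SDs of change (n = 10, t, 9 df).**

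| Assumed SD of change (min) | Detectable (min) | Power at 2.85 min |
|---|---|---|
| 2 | 2.0 | 98% |
| 3 | 3.0 | 76% |
| 4 | 4.0 | 52% |
| 6 | 6.0 | 27% |
| 11.5 | 11.5 | 11% |

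**The case against.** The best reply is that 11.5 min is probably not an SD of within-person change. It matches the two condition SDs pooled, and it comes from a study with mean times of 11.6 and 21.9 min, whereas this trial targets 3–8 min. The true SD of change here could be much smaller, and at 2 to 3 min the trial would have 98% to 76% power for 2.85 min. On this view the power is unknown rather than 11%, and printing 11.5 min as the detectable difference would preserve a doubtful input.

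That is fair, and it limits the conclusion: the 11% figure, the 130 participants and the comparison with the length of the test all depend on the stated SD. It does not rescue the sentence, which says that 2.85 min results from applying 11.5 min as the SD of change.

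Two supporting points depend on the method. That no correlation reproduces 2.85 min from the cited SDs holds for the t calculation only. So does the statement that the detectable difference exceeds the 10.3 min gain in the source study, since the normal approximation gives 10.2 min.

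It can also be said that 2.85/8 = 36% and 2.85/3 = 95% are correct arithmetic, and that 171 s does exceed 105 s. Both are true. What lacks support is that 10 participants can detect such a difference.

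Finally, the sample was set by feasibility and enrolment has begun, so neither conduct nor sample size would change. That bears on the cost of correction, not on whether the statement is right.

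**Conclusion.** The concern holds. On the inputs as printed, the detectable difference is about 11.5 min (10.2 min by normal approximation), roughly four times the stated 2.85 min, and power at 2.85 min is about 11%. This assumes 10 complete pairs, an SD of change of 11.5 min, and a two-sided test at 0.05. Losses make it worse: at the same SD, 9 completers give 12.3 min and 8 give 13.3 min.

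The actual power is not known, because the document gives no usable estimate of the SD of within-person change in this population. The claim of 80% power at 2.85 min is therefore unsupported. So is the conclusion that the feasible sample can show a plausible and clinically meaningful effect. This must be corrected, since that conclusion is the stated justification for the sample.

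**What to change.** Revise the power paragraph in Recruitment and power:

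1. State the SD of within-person change actually used and justify it. If 2.85 min came from an SD of about 2.86 min, say so and give its source in place of 11.5 min. If 11.5 min stands as the SD of change, report a detectable difference of about 11.5 min (11.6 min with the period term).
2. Add that with 10 pairs the detectable difference is about one SD of the change, and show it over a range such as 2 to 11.5 min.
3. Withdraw the statements that the detectable difference is clinically meaningful and equals 36–95% of test time, unless the justified SD supports them. The comparison of 171 s with 105 s can stay as a remark on clinical relevance.
4. It would help to add that a non-significant result whose confidence interval includes 105 s is inconclusive. This guards interpretation and is not part of correcting the arithmetic.

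The cost is one rewritten paragraph and, unless a smaller SD can be justified, a less favourable power statement. Sample size, recruitment, test conduct and the planned analysis do not change.
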